## Abstract

**Background::**

To treat functional constipation, both electroacupuncture (EA) therapy and transcutaneous electric nerve stimulation (TENS) are safe and effective. However, no head-to-head comparison trial has been conducted. This trial compares the efficacy of electroacupuncture relative to transcutaneous electric nerve stimulation for functional constipation.

**Methods::**

Individuals with functional constipation will be randomly allocated to receive either EA or TENS (n = 51, each), 3 times per week for 8 weeks. The primary outcome is the percentage of participants with an average increase from baseline of 1 or more complete spontaneous bowel movements at week 8. The secondary outcome measures are the following: at the time of visits, changes in the number of complete spontaneous bowel movements, number of spontaneous bowel movements, stool character, difficulty in defecation, patients’ assessment of quality of life regarding constipation (self-report questionnaire), and use of auxiliary defecation methods.

**Discussion::**

The results of this trial should verify whether EA is more efficacious than TENS for relieving symptoms of functional constipation. The major limitation of the study is the lack of blinding of the participants and acupuncturist.

## Introduction

1

Functional constipation is a common chronic gastroenteric disease. According to epidemiological data, the prevalence of constipation in the worldwide population is 0.7% to 79.0%, and 19.2%, 19.7%, and 10.8% in Europe, Oceania, and Asia, respectively.^[1]^ There are currently 3 broad categories of therapies for functional constipation: nonpharmaceutical, pharmaceutical, and surgical. The most widely applied therapy is nonpharmaceutical, via lifestyle adjustment to establish good habits of defecation. Pharmaceutical treatments are used to relieve symptoms, but constipation tends to recur,^[2,3]^ and the side effects of most medications cannot be ignored.^[4–6]^ Surgical treatment has strict indications and is performed only in exceptional cases ^[7]^ or reserved for extreme cases of colonic inertia;^[8]^ surgery to treat constipation is not routine.

In recent years, acupuncture to correct constipation has attracted attention. A systematic review showed that acupuncture is effective for this purpose.^[9]^ In addition, a multicenter randomized controlled trial involving 1075 subjects showed that electroacupuncture (EA) was safe and effective for chronic severe functional constipation.^[10]^

To treat constipation, transcutaneous electrical nerve stimulation (TENS) delivers a targeted electrical current to specific areas or the spinal ganglion segment of the body surface that regulates peristalsis of the colon.^[11]^ According to a systematic review, TENS can accelerate colonic transit and has a certain therapeutic effect on functional constipation.^[12]^

Theoretically, the therapeutic effect of EA for treating constipation may be better than that of TENS, since the latter stimulates only the skin, while the EA needle delivers current at a deeper level. TENS may be less able than EA to overcome the electrical resistance of the skin, subcutaneous tissues, and muscles.

In this study, we will compare the efficacy and safety of EA relative to TENS (control) for the treatment of functional constipation.

## Methods

2

### Study design

2.1

This is a randomized parallel-group controlled trial. The flowchart and time point of the trial assessment are presented in Figs. 1 and 2, respectively. The trial protocol conforms to the principles of the Declaration of Helsinki and has been approved by the Ethics Committee of Guang’anmen Hospital of China Academy of Chinese Medical Sciences (2017-059-KY-01). All modifications of this protocol will be submitted to the Ethics Committee of Guang’anmen Hospital. And this trial has been registered at clinical trials.gov (NCT03391635). All eligible participants will be required to provide a sign informed consent before being randomly allocated.

**Figure 1 F1:**
[figure not shown]
Study design schedule-time frame of the trial.

**Figure 2 F2:**
[figure not shown]
Standard protocol items: recommendations for interventional trials (SPIRIT).

### Study setting and recruitment

2.2

This study will be conducted from July 2018 to December 2020 in Guang’anmen Hospital, China Academy of Chinese Medical Sciences. A total of 102 participants with functional constipation will be recruited openly through posters, hospital websites, and networks. A postgraduate is responsible for consultation with the participants and screening, filling out the screening form, recording demographic data, history of diagnosis and treatment, inclusion and exclusion criteria, and other basic data of the participants. The qualified participants will undergo a baseline evaluation for 1 week.

For inclusion in this study, participants will conform to the following criteria: with functional constipation as defined by the Rome III criteria;^[13]^ specific symptoms including laborious defecation or <3 times per week, hard stool, a sense of obstruction, needing an auxiliary defecation method; aged 18 to 75 years; volunteered to participate and provided signed informed consent.

Potential participants with any of the following will be excluded from this study: irritable bowel syndrome; organic constipation or secondary constipation caused by endocrine, metabolic, neurogenic, or postoperative diseases; combined with severe heart, liver, or kidney damage; cognitive impairment, aphasia, or mental disorders; inability to cooperate with the examination or treatment; pregnant or lactating; abdominal aortic aneurysm; abnormal enlargement of the liver or spleen; blood coagulation dysfunction or chronic use of anticoagulants such as Warfarin and Heparin; or with an installed cardiac pacemaker.

### Randomization

2.3

The randomization process will be performed using Statistics Analysis System (SAS) software in the office of the clinical drug test agency of Guang’anmen Hospital. The random numbers and groups will be sealed in opaque envelopes for random allocation and concealment. The acupuncturists will obtain the information of the random numbers and group assignment by opening these envelopes.

### Blinding

2.4

The evaluator, data processor, statisticians, and other researchers who are not involved in the treatment process will be blinded to the treatment.

### Interventions

2.5

#### Electroacupuncture (EA) group

2.5.1

The acupoints are bilateral Tianshu (ST [stomach] 25), Fujie (SP [spleen] 14), and Shangjuxu (ST37), according to the classic acupuncture point prescriptions within the Traditional Chinese Medicine system (National Standard of People's Republic of China [GB/T 12346-2006] Nomenclature and Location of Acupuncture Points in 2006).^[14]^

During the EA, the participant is supine. After routinely sterilizing the skin, stainless filiform needles (0.30 × 50 mm or 0.30 × 75 mm, Huatuo Brand, Suzhou Medical Appliance, China) will be inserted into bilateral ST25 and SP14 vertically and slowly until touching the abdominal muscle layer. The bilateral ST37 will be inserted to a depth of 25 to 30 mm with the manipulation of steady small lifting, thrusting, and twirling 3 times, until the subject experiences a sensation of de qi (sourness, numbness, and heaviness). An electric acupuncture apparatus (SDZ-V EA; Huatuo, Suzhou, China) will be applied to bilateral ST25, SP14, and ST37 with a dilatational wave of 2/10 Hz and an electric current intensity of 0.1 to 1.0 mA, depending on the participant's tolerance, with a slight tremor of the participant's muscles.

Each session will last for 30 minutes. Participants will be treated 3 ×/wk for 8 weeks. Each participant will undergo 24 sessions.

#### Transcutaneous electric nerve stimulation (TENS) group

2.5.2

The acupoints, location, and electroacupuncture apparatus of the TENS control group will be the same as for the EA group, the only difference being that the front end of the wire of the electric acupuncture apparatus is changed to a skin electrode patch without acupuncture. The participant will be supine, and the skin routinely sterilized. Skin electrode patches (50 × 50 mm) will be placed on bilateral ST25, SP14, and ST37 with a dilatational wave of 2/10 Hz and an electric current intensity of 2 to 5 mA,^[15,16]^ depending on the participant's tolerance.

The frequency and treatment sessions will be the same as for the EA group.

### Outcome measurement

2.6

#### Primary outcome

2.6.1

The primary outcome is the percentage of participants with an average increase of 1 or more complete spontaneous bowel movements (CSBMs) during the interval from baseline through week 8.

#### Secondary outcomes

2.6.2

The secondary outcome measures are the following 7 items: percentage of participants with an average increase from baseline of at least 1 CSBM at weeks 4, 20, and 32; change in the number of CSBMs at weeks 4, 8, 20, and 32; change in the number of spontaneous bowel movements (SBMs) at weeks 4, 8, 20, and 32; percentage of participants with type 3 or type 4 stool at weeks 4, 8, 20, and 32, as defined by the Bristol scale;^[17]^ change in average score for difficult defecation at weeks 4, 8, 20, and 32; change in total score on the PAC-QOL questionnaire ^[18]^ at the end of week 8, relative to baseline; and the percentage of participants using cathartics, and the average amount of cathartics, at weeks −1, 4, 8, 20, and 32.

The participants will be asked to record a diary of defecation every day during weeks −1, 4, 8, 20, and 32 after randomization. The recordings are to include bowel movements, SBMs, CSBMs, the stool character, degree of difficulty in defecation, and the use of auxiliary defecation methods. All adverse events that occur during the trial will be recorded. Serious adverse events should be reported to the principal investigator immediately.

The participants’ expectations will be assessed before the intervention with 4 brief questions for which the answers chosen may be “Yes,” “No,” or “Unclear,” as follows: “Do you think EA is effective for treating illness?”; “Do you think EA will help improve your symptoms?”; “Do you think TENS is effective for treating illness?”; “Do you think TENS will help improve your symptoms?”. In addition, a fifth question (“Which kind of treatment do you prefer?”) may be answered as “EA,” “TENS,” or “Does not matter.”

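### The Bristol stool-form outcome is a follow-up status with no week −1 reference, so its percentages cannot be read as normalisation and the planned test leaves baseline stool form unused

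*Protocol article*

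**What the plan says.** Section 2.6.2 fixes the measure, the threshold and the weeks: "percentage of participants with type 3 or type 4 stool at weeks 4, 8, 20, and 32, as defined by the Bristol scale". The other secondary outcomes are tied to baseline in some way. The responder outcome is "percentage of participants with an average increase from baseline of at least 1 CSBM at weeks 4, 20, and 32". The CSBM count, the SBM count and PAC-QOL are changes, and so is the straining item: "change in average score for difficult defecation at weeks 4, 8, 20, and 32". Cathartic use is a status, but week −1 is listed: "the percentage of participants using cathartics, and the average amount of cathartics, at weeks −1, 4, 8, 20, and 32".

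The baseline information will exist. Participants keep a diary in week −1 as well as in the follow-up weeks ("The participants will be asked to record a diary of defecation every day during weeks −1, 4, 8, 20, and 32 after randomization"), and stool character is among the entries ("The recordings are to include bowel movements, SBMs, CSBMs, the stool character, degree of difficulty in defecation, and the use of auxiliary defecation methods").

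For entry, section 2.2 requires Rome III functional constipation and "specific symptoms including laborious defecation or <3 times per week, hard stool, a sense of obstruction, needing an auxiliary defecation method". No Bristol type and no week −1 diary cut-off is set. Section 2.7.2 names rank-sum or χ² tests for comparing the two groups and mentions no use of baseline values.

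**The concern.** A participant can have functional constipation because of straining or infrequent stools while passing stools of type 3 or 4. Section 2.2 puts hard stool in a symptom list whose and/or structure is unclear, so such a person is not clearly excluded. On this outcome that person has no room to improve, yet is scored a success at each visit where the form is still type 3 or 4.

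Three things follow:

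- A figure such as 50% at week 8 cannot be read as the share whose stool form normalised.
- The contrast between arms may be weakened.
- A chance difference between arms in baseline stool form feeds into an unadjusted comparison, although the data to remove it are already being collected.

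**Working it through.** **The plan's own figure.** Section 2.7.1 sizes the trial on the primary outcome: 70% versus 40%, two-sided 5%, 80% power. The pooled-variance formula for two proportions without continuity correction gives 42 per group, as stated. For the 20% loss, 42 × 1.2 = 50.4, rounded up to 51, also as stated. None of this depends on stool form, for which the article gives no rates and makes no power claim.

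**Formula.** Let b be the share at type 3 or 4 in week −1, r₁ and r₂ the probabilities that they are still at type 3 or 4 at a follow-up visit under EA and TENS, and q₁ and q₂ the probabilities that the others reach it. The analysed difference is

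D = b(r₁ − r₂) + (1 − b)(q₁ − q₂).

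With r₁ = r₂ this is (1 − b)(q₁ − q₂).

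**Inputs.** The document gives only n: 51 randomised per arm, and 42 as the calculated size before the allowance for loss. All rates are assumptions: b from 10% to 40%; r = 85% in both arms; q₁ = 55% and q₂ = 30% (a true 25-point effect); and q = 10% in both arms for the no-effect case.

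**Success rate with no treatment effect.** 0.85b + 0.10(1 − b) = 17.5%, 25%, 32.5% and 40% at b = 10%, 20%, 30% and 40%.

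**Difference and power with equal retention, 51 per arm** (simulated, two-sided 5%):

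| b | D = (1 − b) × 25 | Unadjusted χ² | Cochran-Mantel-Haenszel by week −1 status |
|---|---|---|---|
| 10% | 22.5 points | 66% | 66% |
| 20% | 20.0 points | 56% | 58% |
| 30% | 17.5 points | 46% | 49% |
| 40% | 15.0 points | 36% | 40% |

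Stratifying adds about 0 to 4 points of power. With 42 per arm the change is about −1 to +3 points. Most of the loss comes from having fewer participants who can improve, and no stratified test restores that.

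**Unequal retention.** With r₁ = 90% and r₂ = 65%, D = 25b + 25(1 − b) = 25 points for every b, and unadjusted power stays at about 75%. The difference does not shrink at all.

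**Chance imbalance.** The standard deviation of the between-arm difference in baseline share is √(2b(1 − b)/n). At n = 51 this is 5.9, 7.9, 9.1 and 9.7 points for b = 10% to 40%. Under the no-effect rates each point of imbalance moves the success difference by 0.85 − 0.10 = 0.75 point. At b = 20%, one standard deviation therefore moves it by 0.75 × 7.9 ≈ 5.9 points.

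**Whether redefining success would help.** Under a second set of assumed rates (70% versus 40% among those not at type 3 or 4 at entry, full retention, 42 per arm, b = 20%), the bare status gives 63% power. Counting only new type 3 or 4 over everyone randomised gives 60%. Restricting to those not at type 3 or 4 at entry (34 per arm) gives 71%. A percentage of new normalisation should therefore use the restricted denominator.

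**The case against.** The strongest reply is that a status proportion at fixed visits is a legitimate endpoint. Randomisation makes the comparison valid, chance imbalance is random error that the test already allows for, and whether a secondary binary outcome is stratified by baseline is often left to a full protocol or SAP that is not shown. Cathartic use is also a status. Section 2.2 read conjunctively would require hard stool, and then b could be near zero.

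Most of this stands, and it limits the point. A reader might infer that participants with type 3 or 4 stool in week −1 are successes at every visit. They are not: form is scored visit by visit, and a stool that has hardened counts as a failure. A reader might also infer that the EA–TENS difference is certainly diluted, or biased. The document gives neither the baseline share nor the retention in each arm, and the unequal-retention case shows no dilution. Nor does it support a claim that such participants definitely enter, only that they are not clearly kept out. How several stools in a week become one status is not stated either, so b has no known size.

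What the reply does not remove is the contrast within section 2.6.2. The article goes beyond silence: it fixes this outcome's weeks, omits week −1, and lists week −1 for cathartics in the same sentence. As fixed, the outcome does not show normalisation, and the named tests leave an available baseline value unused.

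**Conclusion.** The point holds as a minor one. Stool form is defined without a baseline reference, unlike its sibling outcomes, and entry with type 3 or 4 stool is not clearly ruled out, so the reported percentages cannot be read as normalisation. Attenuation by (1 − b) is conditional on an unknown b and on similar retention in the two arms: 25 points would become 22.5 to 15 for b of 10% to 40%, and would remain 25 with retention of 90% versus 65%. All these rates are assumptions. There is no bias in the randomised comparison and no effect on the primary outcome or on the 42 and 51 per group. The case for change rests on interpretability and on protection from chance baseline imbalance, with little power to be gained.

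**What to change.** In section 2.6.2, add week −1 to the stool-form outcome and report the type 3 or 4 percentage by arm at that week, as is done for cathartics. For weeks 4, 8, 20 and 32, replace the unadjusted χ² test with a Cochran-Mantel-Haenszel test stratified by week −1 status, or with a model adjusted for it. Derive week −1 status by the same weekly rule as at follow-up. Alongside, report the percentage newly reaching type 3 or 4 among those without it at week −1, using only those participants as the denominator.

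The cost is a sentence or two of outcome wording and one stratified analysis of diary data already collected, with no added visits or participants. The drawback is that the newly-reaching percentage rests on fewer participants: with 42 per arm and b of 20%, about 34.

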#### Statistical analysis

2.7.2

The statistical analyses will be performed using the SPSS 20.0 statistical software. Continuous data will be represented by the mean, standard deviation, median, minimum value, and maximum value. Categorical data will be represented by percentage. For the data with normal distribution, the *t* test or rank-sum test will be used for continuous data, and a nonparametric test or *χ*^2^ test for categorical data. A rank-sum test or *χ*^2^ test will be used to analyze the difference between 2 independent samples. Statistical analyses will be 2-sided tests. A *P* value <.05 will be considered statistically significant.

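### The cathartic-use secondary outcome lists the baseline week as an outcome time point and has no baseline reference; use week −1 as baseline and adjust later comparisons for it (minor)

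*Protocol article*

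**What the plan says.** Secondary outcomes (2.6.2) lists seven items. The last covers the share of participants who use cathartics and "the average amount of cathartics, at weeks −1, 4, 8, 20, and 32".

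Study setting and recruitment (2.2) identifies week −1: "The qualified participants will undergo a baseline evaluation for 1 week".

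The other six items are worded differently, and none lists week −1:

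- Responders: "percentage of participants with an average increase from baseline of at least 1 CSBM at weeks 4, 20, and 32".
- CSBMs: "change in the number of CSBMs at weeks 4, 8, 20, and 32".
- SBMs: "change in the number of spontaneous bowel movements (SBMs) at weeks 4, 8, 20, and 32".
- Stool form: "percentage of participants with type 3 or type 4 stool at weeks 4, 8, 20, and 32". This is a raw percentage, but it starts at week 4.
- Difficulty of defecation: "change in average score for difficult defecation at weeks 4, 8, 20, and 32".
- PAC-QOL: change in total score at the end of week 8 relative to baseline.

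Statistical analysis (2.7.2) names t, rank-sum and χ² tests. It says that a rank-sum or χ² test "will be used to analyze the difference between 2 independent samples", two-sided, with P < .05 as the criterion. It mentions no baseline term.

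**The concern.** A value recorded before treatment cannot show a treatment effect, so week −1 does not belong among the time points of an efficacy outcome. Its proper use is as the reference for the later weeks. The cathartic item does not state that use: it puts the baseline value in the same list as the results and does not define the later values against it.

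Cathartic use probably persists within a person. If the arms differ by chance at week −1, part of that difference will still be present at weeks 4 to 32, and a raw two-sample comparison cannot separate it from a treatment effect. The comparison also leaves in the variance that the week −1 value could explain. At stake is the precision of one secondary outcome and its protection against a chance imbalance.

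**Working it through.** The plan gives no figure of its own on this point. The check has three parts.

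**1. Where week −1 enters.** Counting outcome-by-time-point pairs in Secondary outcomes: responders 3, CSBM 4, SBM 4, stool form 4, difficulty 4, PAC-QOL 1, cathartics 2 measures × 5 weeks = 10. The total is 3 + 4 + 4 + 4 + 4 + 1 + 10 = 30. Two of these, both cathartic, fall at week −1. With week −1 as baseline only, 28 post-baseline pairs remain, 8 of them cathartic.

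**2. Size of a chance baseline gap.** The input is 51 per group (Sample size, 2.7.1). In SD units the standard error of the baseline difference is √(2/51) = 0.198, so the 95% range is ±1.96 × 0.198 = ±0.39 SD. With the 42 per group that the article plans for before its dropout allowance, the figures are √(2/42) = 0.218 and ±0.43 SD.

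**3. What carries forward, and what adjustment gains.** The documents give no within-person correlation ρ, so 0.3, 0.5 and 0.7 are assumed. The model is bivariate normal with no treatment effect.

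- Carried gap = ρ × baseline gap.
- Conditional type I error of the unadjusted later test, given a baseline z-score b, is 1 − Φ[(1.96 − ρb)/√(1 − ρ²)] + Φ[(−1.96 − ρb)/√(1 − ρ²)].
- Variance after linear adjustment = 1 − ρ² of the unadjusted variance.
- Variance of a simple change score, with equal variances at both times, = 2(1 − ρ) of the unadjusted variance.

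| ρ (assumed) | Carried from a 0.39 SD gap | Type I, b = 0 | Type I, b = 1 | Type I, b = 1.96 | Variance, adjusted | Variance, change score |
|---|---|---|---|---|---|---|
| 0.3 | 0.12 SD | 4.0% | 5.0% | 7.9% | 0.91 | 1.40 |
| 0.5 | 0.19 SD | 2.4% | 4.8% | 12.9% | 0.75 | 1.00 |
| 0.7 | 0.27 SD | 0.6% | 3.9% | 20.5% | 0.51 | 0.60 |

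For ρ = 0.5 and b = 1.96, the first term is 1 − Φ[(1.96 − 0.98)/0.866] = 1 − Φ(1.13) = 0.129. The second term is about 0.0003.

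The conditional error is below 5% when the arms happen to be balanced and above it after a large gap. Averaged over all randomisations it is 5%, and the unadjusted estimate is unbiased. Adjustment removes ρ² of the variance: 9%, 25% or 49%. A change score gains nothing at ρ = 0.5 and loses precision below it, which is why adjustment is the better remedy.

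**The case against.** The strongest reply is that week −1 may be listed only to show the reference value. The five weeks are exactly the diary weeks given in the next paragraph of the article. Items worded as changes already contain the baseline, whereas a raw percentage or amount needs it shown beside the later values. Unadjusted two-sample tests are valid in a randomised trial, and covariate adjustment is commonly left to an analysis plan, which is not shown here. Most of this stands, and it rules out several stronger readings:

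- **That week −1 will be tested between arms.** A reader might infer this from the outcome list and the P < .05 rule, but no sentence says that every listed time point is tested or that week −1 is. A false-positive figure of 1 − 0.95² = 9.75% for two baseline tests needs that inference. It also needs independence, which is implausible because non-users have an amount of zero.
- **That a chance gap passes undiminished into weeks 4 to 32.** Only the fraction ρ carries over, and the overall type I error stays at 5%.
- **That listing week −1 causes the carry-over.** Deleting it would change nothing by itself. The stool-form item is also a raw percentage with no baseline term, and it does not list week −1.
- **That large gaps in the share of users would often be declared significant.** If 50% use cathartics (assumed), the standard error is √(2 × 0.5 × 0.5/51) = 9.9 points. A gap of 10 points or more then has a probability of about 31%, but 10 points is only z = 1.01; significance needs about 19 points. At 20% or 10% users the probability is about 21% or 9%.

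The reply leaves one thing unanswered. As written, the article names a pre-treatment week as a time point of an efficacy outcome and does not say that it is the reference for the later weeks.

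**Conclusion.** The point holds as a minor correction to one of seven secondary items. It rests on the wording of the outcome definition, not on the absence of a full analysis plan. The unadjusted comparisons at weeks 4, 8, 20 and 32 are not invalid. They are less precise than they could be, and they are exposed to conditional error if the arms happen to differ at baseline.

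The size depends on a correlation that the documents do not give and on a linear, normal model. Cathartic amounts with many zeros may follow that model poorly, so the variance and error figures indicate an order of magnitude and are not predictions. The primary outcome and the sample size are untouched.

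**What to change.** - Label week −1 as baseline only, and report cathartic use and amount there descriptively by arm, without a test.
- Keep weeks 4, 8, 20 and 32 as the outcome time points.
- Compare both measures at those weeks adjusted for the week −1 value. For use, fit a logistic regression on arm and week −1 use, with the result standardised to a risk difference so that it still answers a question about percentages. For amount, use a baseline-adjusted or rank-based ANCOVA.
- Reword the diary sentence in Secondary outcomes, which counts week −1 among the weeks after randomisation.

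The cost is a line or two of text and a slightly longer analysis, using a value that the trial already collects. If few participants use cathartics, the logistic model may be sparse or show separation, so a fallback, such as the unadjusted comparison, should be named in advance.
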